### Measures and Tasks

#### Anxiety

Anxiety will be measured using the Spence Children’s Anxiety Scale [25], a self-report assessment of specific anxiety symptoms in children aged 8-11 years, categorized as social phobia (6 items), panic or agoraphobia (9 items), generalized anxiety (6 items), obsessive-compulsive (6 items), separation anxiety (6 items), and physical injury fears (5 items). Children respond using a 4-point Likert scale from 0=never to 3=always. Anxiety symptoms will be examined separately (eg, social phobia, and separation anxiety) in addition to the inspection of change in an overall anxiety score calculated by summing the 38 items. Higher scores represent higher symptoms of anxiety.

#### Worry

Worry will be assessed using the Penn State Worry Questionnaire for Children [26], a 14-item questionnaire that measures the tendency to engage in excessive, generalized, and uncontrollable worry in children aged 7-17 years. Items are rated on a 4-point Likert scale from 0=never to 3=always. Total worry scores are calculated (after reversing 3 items) by summing the scores on all items and range from 0 to 42; higher scores represent a greater tendency to worry.

#### Depression

Depression will be indexed by the Low Mood subscale from the Revised Children’s Anxiety and Depression Scale [27], a self-report assessment of symptoms of major depressive disorder in children aged 8-18 years. The low mood subscale includes 10 items and children respond using a 4-point Likert scale from 0=never to 3=always. Total scores range from 0 to 30 with higher scores indicative of lower mood.

#### Rumination

The rumination subscale from the Child Response Style Questionnaire [28] will be used to capture repetitive negative thinking or rumination. Children respond to 13 items on a 4-point Likert scale from 0=almost never to 3=almost always. Total scores range from 0 to 39 with higher scores representing greater rumination.

#### Math Anxiety

The Modified Abbreviated Math Anxiety Scale [29] will be used to assess math anxiety. The 9-item self-report measure comprises 2 subscales, math evaluation anxiety (4 items), for example, thinking about a math test the day before you take it, and math learning anxiety (5 items), for example, starting a new topic in math. Children respond to statements asking how anxious they would feel during certain situations involving math using a 5-point Likert scale from 1=low anxiety to 5=high anxiety.

#### Inhibitory Control

A standard (ie, nonadaptive) Go/No-Go Task [30] will be used to measure inhibitory control. The Go/No-Go Task requires children to view visually presented stimuli and inhibit a dominant response based on instructions, for example, press the spacebar when they see a particular target (go) but do not press the spacebar when they see a different target (no-go). The task captures accuracy and reaction time (RT).

#### Shifting

The Color Shape-Shifting Task [31] will be used to assess shifting performance. In this task, children are presented with some colored shapes and are required to sort the stimuli by shape or color, as fast as they can. Children are given letter cues; for example, *S* for shape and *C* for color before each stimulus appears to indicate the characteristic to focus on. The task captures accuracy and RT.

#### Updating

The *n*-back Task [32] will be used to index updating performance. The task requires children to monitor letters presented in blocks of increasing difficulty (ie, *n*) and indicate when presented with a letter seen on the previous trial (1-back), after 1 intervening trial (2-back), or after 2 intervening trials (3-back). Difficulty increases with the number of intervening trials. Children indicate the same or different with a keyboard button press based on the letter 1-, 2-, or 3-back from this letter. The task captures accuracy and RT.

#### Math Achievement

A total of 3 subscales from the Woodcock-Johnson IV Tests of Achievement [33] will be used to assess math achievement, namely, Applied Problems, Calculation, and Math Fact Fluency. Administration and scoring will be consistent with the authors’ manual. To avoid measurement error due to the practice effects, different test forms will be used at each data collection point.

#### Training Groups

We will randomly assign participants to 1 of the 2 training groups. Groups comprise an experimental CCT group that will train using an adaptive Go/No-Go Task (aGo/No-Go) targeting inhibitory control, and an active control group that will train using a low-load task. The active control task does not require the same cognitive load as the aGO/No-Go task; thus, we do not expect it to produce emotional or cognitive changes. Children in both groups will undertake 10 minutes of training per day for 3 weeks, allowing 15 sessions to be completed.

#### Inhibitory Control Training

The aGo/No-Go task requires participants to focus on desired cues related to a continuous stream of blended stimuli and press the spacebar when the desired cue appears and withhold a response when it does not appear (as per Go/No-Go). The adaptive nature of the task adjusts to the child’s performance such that if the child is doing well, the task reduces the time for responding, whereas if the child is having difficulty the task allows more time for responding, thus positively reinforcing success.

#### Active Control Training

The low-load task presents children with a continuous stream of blended stimuli and requires them to identify target items.

### Equipment and Procedure

All assessments and training will be completed on iPads (9th generation, iOS 16, 64GB; Apple Inc) specific to this project. Self-report symptom scales will be hosted on a computer-based survey platform (Qualtrics) such that the participating children can complete them under the supervision of their classroom teacher, during class time. Inquisit cognitive tasks will be deployed (retrieved from Millisecond Test Library). Math achievement tests will be administered 1:1 in a quiet room by the research team. Daily training of the aGo/No-Go and 1-back will be conducted using a computer-based experiment builder (Gorilla Experiment Builder) and include some minor gamification features to improve motivation and engagement. Training will be completed under the supervision of the classroom teacher.

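### The article names the control task in two ways; if it is the 1-back, controls train on one level of the updating outcome and the updating contrast is biased against CCT

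*Protocol article*

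**What the plan says.** All places are in the Methods of the protocol article unless noted.

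- **Training Groups** sets up two arms: "We will randomly assign participants to 1 of the 2 training groups". The CCT arm has the adaptive Go/No-Go. The comparator is "an active control group that will train using a low-load task". Because its cognitive load is lower, the authors write: "thus, we do not expect it to produce emotional or cognitive changes".
- **Active Control Training** describes the task in one sentence: "The low-load task presents children with a continuous stream of blended stimuli and requires them to identify target items". It mentions no memory or comparison rule.
- **Equipment and Procedure** names the trained tasks differently: "Daily training of the aGo/No-Go and 1-back will be conducted using a computer-based experiment builder".
- **Updating** says that the n-back task "will be used to index updating performance". Children must "indicate when presented with a letter seen on the previous trial (1-back), after 1 intervening trial (2-back), or after 2 intervening trials (3-back"). Accuracy and reaction time are recorded.
- **Training dose** is the same in both arms: "Children in both groups will undertake 10 minutes of training per day for 3 weeks, allowing 15 sessions to be completed".
- **Abstract (Results) and Discussion** predict that CCT will improve updating relative to the control group.
- **Data Analytic Plan** tests accuracy and reaction time on the cognitive measures by group and time.

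**The concern.** The comparator gives every between-group contrast its meaning, and a reader cannot tell from the article which task it is. A search for targets in a stream and a 1-back make different demands: the second requires each item to be held and compared with the next one, which is the operation that the updating outcome measures.

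The choice matters most for updating. If controls train on a 1-back, they practise the rule of one outcome level every school day for three weeks, while the CCT arm trains on something else. The trial predicts a CCT advantage on that same outcome. A null or reversed result could then mean that CCT does not transfer to updating, or that the controls were trained on it, and the data would not separate the two.

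**Working it through.** This is a comparison of text. The plan states no figure on this point that could be reproduced.

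**Step 1. Which arm has the 1-back?**
- Number of training groups: 2 (Training Groups).
- Daily training tasks named: adaptive Go/No-Go and 1-back (Equipment and Procedure).
- The adaptive Go/No-Go belongs to CCT (Training Groups).
- Hence the 1-back falls to the control arm. This is an inference by elimination; the article does not say so outright.

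**Step 2. Do the descriptions agree?**

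| Section | Control task |
|---|---|
| Abstract, Study Design, Data Analytic Plan | low-load task |
| Training Groups | low-load task, no emotional or cognitive change expected |
| Active Control Training | identify targets in a stream of blended stimuli |
| Equipment and Procedure | 1-back (by elimination) |

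A 1-back can be low-load, so the label itself does not conflict. The tension is with the target-identification description, which gives no 1-back rule, and with the expectation of no cognitive change. Nothing in the article links the two accounts.

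**Step 3. Overlap with the outcome, if the 1-back stands.**
- Training time per child: 15 sessions x 10 minutes = 150 minutes.
- Outcome levels: 1-back, 2-back, 3-back. Levels sharing the trained rule: 1 of 3.
- CCT training on that rule: none. Both arms also meet the 1-back at the four assessments, but that exposure is equal and cancels.

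**Step 4. Direction.** Write the observed contrast on updating as

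net effect = (true CCT effect) − (control practice gain).

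If practice helps at all, the second term is positive and the contrast shifts against CCT.

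**Step 5. Size.** The documents give neither the practice gain nor a true CCT effect on updating. For illustration only, assume a true CCT effect of 0.20 SD and a range of gains on the updating score:

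| Assumed control gain (SD) | Net effect (SD) |
|---|---|
| 0.10 | 0.20 − 0.10 = 0.10 |
| 0.20 | 0.20 − 0.20 = 0.00 |
| 0.30 | 0.20 − 0.30 = −0.10 |

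The value 0.20 is borrowed from the sample-size statement in Participants, which concerns the primary outcome measures; updating is not identified as one of them. The table shows only that a small effect could be hidden or reversed by a gain of similar size. It does not estimate the bias.

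**The case against.** The strongest reply is that the word 1-back appears as a training task only once, while every other mention of the comparator says low-load task. If it is leftover wording, nothing is contaminated and one word needs correcting. That stands, and it is why the bias has to be stated conditionally.

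A second reply is that the sentence under Active Control Training could be a loose summary of a 1-back, since an n-back also asks for responses to certain items in a stream. This is possible. It would remove the conflict between the task descriptions but not the overlap with the updating outcome.

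A third is that the trained and tested tasks are not shown to be identical. The control task uses blended stimuli and training runs on Gorilla; the outcome n-back uses letters, and the cognitive tasks come from the Inquisit library. This may reduce the practice gain, but the 1-back rule would still be shared.

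Three stronger readings are tempting and are not supported:

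- **A definite shift in SD units.** A reader might assume a gain on the 1-back and divide it by three. The article gives neither a gain nor an equally weighted composite, and the SD of a composite depends on correlations between levels that are not reported.
- **A bias in the anxiety contrast.** The Introduction lists updating among the processes whose training has some support for reducing emotional symptoms. It does not say that a low-load 1-back does so, and Training Groups argues that the control lacks the load. An effect on anxiety is speculative.
- **A risk of a false claim for CCT on updating.** The bias would run the other way.

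**Conclusion.** The concern holds in conditional form. The article does not describe its control task consistently, and this needs correction whichever account is right.

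If Equipment and Procedure is correct, controls receive 150 minutes of training on the rule of one of the three levels of the updating outcome and CCT children receive no such training. The group-by-time test on updating is then biased against CCT, by an amount that cannot be estimated from the documents. This rests on two assumptions: that the 1-back belongs to the control arm, and that practice improves n-back performance to some degree. If the wording is an error, this source of bias disappears.

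A reader might infer that the updating comparison is already shown to be contaminated, or that the trial's main comparisons on anxiety and math are compromised. The text supports neither. Updating is one of several cognitive measures, and the stated objective is anxiety and math achievement. Severity: should-fix.

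**What to change.** 1. Reconcile Training Groups, Active Control Training, and Equipment and Procedure so that one control task is named and described in the same terms throughout.
2. If that task is a 1-back:
   - pre-specify, before analysis, that the updating outcome is 2-back and 3-back performance, for both accuracy and reaction time;
   - report 1-back separately as a trained-task measure for controls;
   - qualify the statement in Training Groups that no cognitive change is expected;
   - state that transfer from 1-back practice to 2-back and 3-back may still bias the updating contrast against CCT. Dropping the trained level does not remove this.
3. If 1-back is an error, correct Equipment and Procedure; no change to the updating score is then needed on this account.

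The cost is a text correction and, in the second case, a scoring rule and the loss of one n-back level from the updating score. The outcome task is presented in blocks by level, so no new data should be needed. The Results section places analysis after data collection ends, so the rule can be fixed before any analysis begins.

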### Data Analytic Plan

Mixed between-within ANOVA will be used with Group (CCT, aGo/No-Go vs active control; low-load task) as the between-subjects factor and time (pre- vs posttraining vs 1- vs 3-month follow-up) as the within-subjects factor. Separate tests will be conducted with the emotional symptom scores, cognitive measures (ie, accuracy and RT), and math achievement scores as dependent variables. Intention-to-treat analyses will be used to account for missing data, as appropriate. Descriptive and inferential statistics will be performed using SPSS (IBM Corp). We will apply Bonferroni corrections to follow-up tests to control for type 1 error.

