**Results:**

We opened enrollment in September 2023. The initial results are expected to be published in late 2024. We predict that children in the CCT group will show a reduction in emotional symptoms; improvements in inhibition, shifting, and updating performance; and advances in math achievement from pre- to posttraining, and that these effects will be maintained at 1- and 3-month follow-ups, compared to children in the active control group.

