### Participants

A nonselect sample of children aged 8-10 years will be recruited from primary schools. An a priori power analysis revealed that 66 participants are required to detect small effects (*d*=0.20) approaching those reported by previous studies with 80% or greater power on primary outcome measures relative to controls [9,23,24]. To allow for approximately 30% attrition we will recruit 100 children proportionately balanced for sex and age across 8, 9, and 10 years. To incentivize enrollment and study completion, participating children will be compensated using monetary tokens redeemed at the end of the study; Aus $ 2.00 (US $1.31) for the completed questionnaires at each of 4 time points and Aus $ 2.00 (US $1.31) for each training session (~Aus $ 40.00; US $26.14 per participant). Given that teachers are required to supervise and monitor the daily training, they will be incentivized for their class’s participation (minimum 20 students) at the rate of 1 teacher relief day for each data collection time point (pre- and posttraining and 1- and 3-month follow-ups).

Primary and P-12 schools, as well as private, independent, and Catholic schools, will be approached regarding participation in the study. A recruitment package of materials (including a university ethics approval letter, gatekeeper permission request, pamphlet, study protocol, participant information sheets for parents, teachers and children, consent forms, and an information sheet about children’s anxiety and depression) will be sent to the school principal to determine interest in participation. Information sessions will be held face-to-face or using a video communications platform (eg, Zoom) for principals, teachers, and parents, as required.

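### The 2×4 ANOVA uses the pretraining score only as change and tests a 3-df interaction; a baseline-adjusted, prespecified contrast would suit the predicted sustained effect better

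*Protocol article*

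**What the plan says.** The Data Analytic Plan in the protocol article states: "Mixed between-within ANOVA will be used with Group" as the between-subjects factor and "time (pre- vs posttraining vs 1- vs 3-month follow-up) as the within-subjects factor". Emotional symptoms, cognitive measures and math scores are each tested separately in this way. On what follows the ANOVA, it says only: "We will apply Bonferroni corrections to follow-up tests to control for type 1 error". The section names no baseline covariate and no primary contrast.

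The Training Groups section randomises participants to the two arms. The Results paragraph of the Abstract predicts improvement from pre- to posttraining and that "these effects will be maintained at 1- and 3-month follow-ups, compared to children in the active control group". The Discussion repeats this prediction.

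The Participants section gives the size: "66 participants are required" for d=0.20 "with 80% or greater power on primary outcome measures relative to controls". It adds: "To allow for approximately 30% attrition we will recruit 100 children".

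**The concern.** Under randomisation the two groups have the same expected pretraining mean. Treating that score as a fourth outcome level makes the model estimate a baseline group difference known to be zero in expectation. The interaction then measures the effect as change from baseline. For the same comparison, change is less precise than covariate adjustment whenever the correlation between visits is below 1.

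The interaction is also sensitive to any departure from parallel profiles. It has the same power for an effect seen only at posttraining, or only at 3 months, as for one sustained across all three visits. The article predicts the sustained pattern. A trial with a small sample could therefore miss the predicted effect when a better-aimed analysis of the same data would have had a better chance of finding it.

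**Working it through.** **Inputs from the article:** d=0.20; N=66 evaluable; 100 recruited with about 30% attrition, so 100 × 0.7 = 70 remaining; four visits; two randomised groups.

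**Assumptions, because the article does not state them:** equal correlation r between all visits (compound symmetry), SD 1, two-sided 0.05, 1:1 allocation. The case d=0.40 is an illustration at twice the protocol's effect.

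**The plan's own figure.** It was not reproduced. A plain two-group comparison at d=0.20 needs 393 per group for 80% power, and 33 per group gives 13%. A repeated-measures interaction with f=0.10, four measures and r=0.5 needs 138. About 66 appears with f=0.10, four measures and r near 0.76–0.77, but in this design f=0.10 corresponds to a sustained d of about 0.46. The figure therefore depends on inputs that the article does not show.

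**Formulas**

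- Interaction: λ = (N/4) × Σ(δₜ − mean δ)² / (1 − r), noncentral F with 3 and 3(N−2) df. Here δₜ is the group difference at each of the four visits. For a sustained effect (0, d, d, d), the sum is 0.75d².
- One-df contrasts: noncentrality = effect / √(4V/N), noncentral t, with V as follows:
  - change at one visit: 2(1−r)
  - adjusted, one visit: 1−r²
  - change to the mean of three visits: (4/3)(1−r)
  - adjusted mean of three visits: (1+2r)/3 − r²

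**Variance ratio, adjusted to change.** For one visit it is (1−r²)/(2(1−r)) = (1+r)/2, which is 0.65, 0.75, 0.85 and 0.90 at r=0.3, 0.5, 0.7 and 0.8. For the mean of three visits it is 0.475, 0.625, 0.775 and 0.85 at the same r.

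**Power at d=0.20, N=66, r=0.5, sustained effect**

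| Test | Calculation | Power |
|---|---|---|
| Interaction, 3 df | λ = 16.5 × 0.03 / 0.5 = 0.99 | 11% |
| Change, posttraining | 0.20 / √(4×1.00/66) = 0.81 | 13% |
| Adjusted, posttraining | 0.20 / √(4×0.75/66) = 0.94 | 15% |
| Change, mean of three | 0.20 / √(4×0.667/66) = 1.00 | 17% |
| Adjusted, mean of three | 0.20 / √(4×0.417/66) = 1.26 | 24% |

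Over r=0.3 to 0.8 the interaction has 9–23% and the adjusted mean 23–39%.

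**Power at d=0.40, N=70, sustained effect**

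| r | Interaction | Adjusted posttraining | Adjusted mean of three |
|---|---|---|---|
| 0.5 | 37% | 48% | 72% |
| 0.6 | 45% | 54% | 77% |
| 0.7 | 58% | 64% | 84% |

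At r=0.5 the unadjusted change contrast for the mean of three has 52%. Of the rise from 37% to 72%, 15 points come from using one degree of freedom and 20 from adjustment.

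The posttraining-only contrast gains 11, 9 and 6 points at r=0.5, 0.6 and 0.7. It gains about 1 point at r=0.8 (78.5% against 77.5%) and loses at r=0.85 (87.9% against 89.0%).

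**Other effect patterns at d=0.40, N=70, r=0.5**

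- Fading (d, d/2, 0): λ = 17.5 × 0.11 / 0.5 = 3.85, so the interaction has 34%; the adjusted mean has 25%.
- Posttraining only: interaction 37%, adjusted mean 14%.
- Emerging late (0, d/2, d): interaction 34%, adjusted posttraining contrast 5%.

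**Sample size for 80% power, sustained d=0.20, r=0.5:** interaction 730; adjusted posttraining contrast 592; adjusted mean of three 330.

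**The case against.** A mixed ANOVA is a standard, valid test of group by time, and this is a proof-of-concept study. Study Design and the Discussion already describe comparisons of pretraining with posttraining and with the follow-ups, so the follow-up tests may recover some of what the omnibus test loses. Contrast details may also sit in a fuller plan. All of this stands, and it makes the point one of efficiency. It does not remove the point, because the article itself fixes the model and the role of the baseline. A follow-up test on change remains less precise than the adjusted one: 13% against 15% in the first table, before any Bonferroni correction.

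Three stronger readings are tempting, and the documents do not support them.

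- A reader might infer that the baseline is wasted. It is not: the interaction uses it as change, and the loss shrinks as r rises.
- A reader might infer that the alternative has no downside. That is nearly true of adjustment, which costs one degree of freedom. It is not true of a targeted contrast, which loses to the omnibus test under patterns it does not target.
- A reader might infer that a significant interaction must precede any follow-up test. That is a common convention, but the article mentions only a correction to follow-up tests and states no such condition.

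**Conclusion.** The point holds as an avoidable inefficiency in a valid analysis. For the predicted sustained effect, the adjusted mean of the three later visits roughly doubles power at r=0.5: 11% to 24% at d=0.20 and N=66, and 37% to 72% at d=0.40 and N=70. It had more power than the interaction at every correlation tried. A posttraining-only contrast gains much less, and nothing at high correlation.

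That adjusting a given contrast for baseline reduces its variance follows from randomisation and holds for any r below 1. The power figures rest on the assumed correlation, compound symmetry, two-sided 0.05 and 1:1 allocation. The advantage over the interaction also requires an effect of roughly the predicted shape.

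The sample-size shortfall remains: even the best of these contrasts needs about 180 to 350 children at d=0.20 as r goes from 0.8 to 0.3.

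**What to change.** For each outcome, fit a repeated-measures mixed model to the posttraining, 1-month and 3-month scores with the pretraining score as covariate, or model all four scores with group means constrained equal at baseline. Before analysis begins, name the primary contrast. The adjusted group difference averaged over the three later visits best matches the prediction. Report the adjusted difference at each visit beside it, so that fading or late emergence is visible. If posttraining alone is the time point of interest, it can be primary, with the smaller gain acknowledged. Keep the group-by-time interaction as a secondary test, and state whether any follow-up test depends on it.

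The cost is a rewording of the analysis plan and one degree of freedom for the covariate; the pretraining scores are already collected. The price of naming one contrast is lower power under patterns it does not target, which is the reason to retain the interaction.

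### The planned four-occasion ANOVA drops children with any missing score, and the intention-to-treat sentence relied on to handle missing data cannot do so

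*Protocol article*

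**What the plan says.** The Data Analytic Plan of the protocol article fixes the model: "Mixed between-within ANOVA will be used with Group (CCT, aGo/No-Go vs active control; low-load task) as the between-subjects factor", with "time (pre- vs posttraining vs 1- vs 3-month follow-up) as the within-subjects factor". Separate tests are run for the emotional, cognitive and math outcomes, in SPSS. The only provision for incomplete data is: "Intention-to-treat analyses will be used to account for missing data, as appropriate". The article names no imputation method, no likelihood-based model and no assumption about why data are missing.

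The Participants section says that "An a priori power analysis revealed that 66 participants are required to detect small effects" (d=0.20) "with 80% or greater power on primary outcome measures relative to controls", and then: "To allow for approximately 30% attrition we will recruit 100 children". It does not divide that attrition by visit or by arm.

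**The concern.** Two features of the plan fit together badly.

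- **The model needs complete rows.** A standard repeated-measures ANOVA with four levels of time uses a child's data on an outcome only if all four scores are present. A child assessed before and after training but absent at 3 months drops out of the whole test for that outcome, including its pre-to-post part. Pre-to-post change is part of the study's main prediction.
- **The stated remedy is not one.** Intention-to-treat means that all randomised children are analysed in the group to which they were assigned. It does not say what to do when a score does not exist. The sentence gives it a function that it lacks.

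Two things are at stake. Precision is lost because scores already collected are not used. The comparison is also exposed to selective loss, because recruiting more children replaces numbers but does not make those who remain comparable between arms.

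**Working it through.** **Inputs from the article.** 100 recruited, about 30% attrition, 66 required, target d=0.20 (Participants); two groups, four time points, mixed ANOVA in SPSS (Data Analytic Plan). Equal allocation, 50 per arm, is assumed because the ratio is not stated.

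**1. The plan's own inflation.** 66 / (1 - 0.30) = 94.3, rounded up to 95; the plan recruits 100. At 30% attrition, 100 × 0.70 = 70 children remain, which exceeds 66. The recruitment figure therefore covers the loss in numbers. How the 66 was obtained is a separate matter and is not used here.

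**2. Children left in the ANOVA.** If attrition means that 30 children lack at least one later score, listwise deletion leaves about 70 of 100. The count depends on the pattern of loss. If visits were instead missed intermittently and independently (an assumption):

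- 5% missing at each of four visits leaves 0.95^4 = 0.81, or 81 of 100;
- 10% missing at each visit leaves 0.90^4 = 0.66, or 66 of 100.

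**3. Precision.** Suppose 90 of 100 are seen posttraining (assumed) and 70 complete all visits. For a between-group comparison at that visit, the ratio of standard errors is sqrt(90/70) = 1.13, so the completer standard error is about 13% larger than the data require.

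**4. Bias of the completer pre-to-post contrast.** Assumptions: no true effect, unit-variance scores, correlation r between baseline and posttraining, and 30% dropout per arm after the posttraining visit. The log-odds of dropout rise by b per SD of the posttraining score, where a higher score means more anxiety. Dropout depends only on the posttraining score, so the expected baseline score of a retained child is r times that child's posttraining score. Hence

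bias = (1 - r) × (mean posttraining score of retained CCT children - the same mean in controls).

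With 30% dropout, numerical integration gives a retained mean of -0.253 SD for b=1, -0.143 SD for b=0.5, and 0 for random dropout.

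| Dropout slope, CCT / control | r=0.6 | r=0.8 |
|---|---|---|
| 1 / random | 0.4 × (-0.253) = -0.10 | 0.2 × (-0.253) = -0.05 |
| 0.5 / random | 0.4 × (-0.143) = -0.06 | 0.2 × (-0.143) = -0.03 |
| 1 / 0.5 | 0.4 × (-0.253 + 0.143) = -0.04 | 0.2 × (-0.253 + 0.143) = -0.02 |
| 1 / 1 | 0.00 | 0.00 |

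Simulation agrees: at r=0.6 with slopes 1 / random, 4,000 trials gave -0.097 SD for completers and 0.003 SD with all posttraining scores used. That second figure assumes that all 100 children are seen posttraining. It is a different scenario from the 90 in step 3, and the two should not be combined.

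**5. Later visits.** A further simulation (r=0.8, dropout in the CCT arm of about 32% with slope 1.5, random 30% in controls) gave a completer bias at the last visit of +0.06 SD when correlation decays with time and 0.00 when it is constant. The direction at follow-up therefore cannot be predicted from the article.

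**The case against.** The strongest reply is that the article states an intention not to restrict the analysis to completers, and that an article may leave the choice of imputation to the full plan. Part of this stands. A reader might infer that the ANOVA and intention-to-treat sentences contradict each other outright. They do not: an ANOVA on multiply imputed data for all randomised children would satisfy both, and the words "as appropriate" leave room for that. What does not stand is that this is only missing detail. The article fixes a model that deletes incomplete cases by default, and it credits intention-to-treat with something it cannot do.

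Three other stronger readings are tempting and are not supported.

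- **That the sample size proves a completer analysis.** Inflating recruitment for attrition is routine under any model, including a mixed model. The Participants section speaks of participants required, not of completers analysed.
- **That the group-by-time effect is biased, by half the target.** Dropout related to outcome is not enough; it must also differ between arms. The -0.10 SD figure is the upper end of the range, and the same mechanism in both arms gives zero. Both groups train for the same time, under the same teacher supervision and for the same payment, so nothing in the article points to strongly differential dropout.
- **That exactly 70 children enter every contrast.** Attrition is approximate, deletion is per outcome, and the article does not say whether the Bonferroni-corrected follow-up tests would use available pairs.

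**Conclusion.** The point holds in this form. The missing-data sentence relies on a principle that does not handle missing data, and it stands beside a model that in standard SPSS use excludes incomplete children. Unless an unnamed imputation step is added, about 70 of 100 randomised children would be analysed at the plan's own attrition, and scores already observed would be discarded. The standard error is about 13% larger posttraining if 90 are seen then.

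Any bias is conditional. Under no true effect, r of 0.6 to 0.8, 30% dropout and log-odds of 0.5 to 1 per SD in one or both arms, it runs from 0.00 to -0.10 SD. Against d=0.20 that is from nothing to half the effect sought (0.10 / 0.20), in the direction of a false benefit. These scenarios are assumptions; the article gives no dropout by arm, visit or score. The listwise deletion and the misuse of the term do not depend on them.

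**What to change.** - **Main analysis.** Use a likelihood-based linear mixed model for repeated measures (SPSS MIXED) with group, time and group-by-time and an unstructured covariance. Include every available observation from all randomised children, as randomised. Multiple imputation before the planned ANOVA is an acceptable alternative and keeps the named model.
- **Assumption.** State that the main analysis is valid if data are missing at random given the observed scores.
- **Sensitivity.** Keep the completer ANOVA as a sensitivity analysis.
- **Wording.** Let the intention-to-treat sentence define the analysis set only: all randomised children, in their assigned group. Describe the missing-data method in a separate sentence and drop the open qualifier.

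The cost is a change to the analysis text, with the same software and no new data. The Results section says that analysis starts only once data collection is complete, so the method can be settled before then. The downside is that results rest on missing at random, which cannot be verified from the data; it is still a weaker assumption than the completer ANOVA needs.
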